#### Data analysis

The SPSS (version 23.0) is used for data management and statistical analysis. The kolmogorov-Smirnov test is used for normality test. The normality data are expressed as mean ± standard deviation, and the skewness data are expressed as median and quartile spacing. An intention-to-treat analysis will be used to assign participants whether or not they complete the intervention. Lost result data will be processed using a mixed-mode approach. Each protocol is then analyzed, including only subjects who completed all outcome measures and followed the intervention protocol. One-way analysis of variance (ANOVA) or nonparametric tests wil be used to compare baseline differences between groups. The effects of training are evaluated using a 22 ANOVA (group × time). Using either a paired T-test or a nonparametric test, differences in each group of variables over time (from baseline to three months) will be evaluated. To detect differences between categorical variables, the Chi-square test will be applied. P values less than 0.05 are considered significant.

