## Abstract

**Introduction:**

In this study, we will combine the traditional Baduanjin with Yijin Jing and Wuqinxi to create an optimized Baduanjin exercise program with three different forms (vertical, sitting, and horizontal) to adapt to idiopathic pulmonary fibrosis (IPF) patients in vairous stages of the disease. The purpose of this study is to explore and compare the therapeutic effects of this multi-form Baduanjin, traditional Baduanjin, and resistance training on lung function and limb motor function in IPF patients. The goal of this study is to prove a novel optimal exercise prescription strategy of Baduanjin exercise for improving and protecting lung function in IPF patients.

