### Sample size

6MWT is the most commonly used outcome indicator in pulmonary rehabilitation (PR) and can be used for sample size estimation. In 6MWT, the minimum difference (miniDIFF) between different groups is 54 m, and the baseline standard deviation (SD) is 57 m. Given a two-tailed 0.05 and a power of 80%, the minimal sample size for each group is 19. To compensate for the expected loss of participants, an adjusted sample size of 27 could be acquired for each group, and 140 patients could be recruited, assuming a roll-out rate of 30%.

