### Randomization and concealed allocation

Prior to the baseline assessment, participants will be randomized into five groups: CG, IG, TG, RG, and IRG. The allocation sequence will use “study randomized” transcendental prior distribution, the random number generator is (https://www.randomizer.org/) online random number generator, and the participation of participant recruitment assessment or not engage in the researchers. Concealed allocation will be achieved using sequentially numbered, sealed, and opaque envelopes kept in security cabinets that can only be opened by specifically authorized staff.

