### Outcome measurement

Outcomes will be measured at two-time points (within 1 week and after 3 months) for participants who complete baseline enrollment. Primary prognostic indicators included Lung function and 6MWT. Secondary outcome measures included mMRC, HRCT, and the questionnaire.

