#### Assessments of basic characteristics

The patient will undergo lung function tests under the supervision of medical staff. TLC, VC, DLco, and min•mmHG are recorded in detail after the test [28, 29], while the lung function assessment table contains three levels (effective, stable, and ineffective) for qualitative assessment according to different values of TLC, VC, DLco, and min •mmHG.

The evaluation is based on the dyspnea scale (mMRC) developed by the British Medical Research Council [30]. The medical staff instructed the patients to complete the questionnaire according to protocol, and the patients are evaluated at the conclusion of the experiment. Each subject’s dyspnea level is meticulously recorded and categorized into three distinct categories. The severity of dyspnea increases as the dyspnea score rises.

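### Five arms and at least two primary outcomes are judged at one flat 0.05, with no primary comparison, gate or adjustment, and the 2 × 2 ANOVA does not fit five arms

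*Protocol article*

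**What the plan says.** **Arms and aim.** Under Randomization and concealed allocation, "participants will be randomized into five groups: CG, IG, TG, RG, and IRG". The abstract's aim is to "explore and compare the therapeutic effects of this multi-form Baduanjin, traditional Baduanjin, and resistance training", so comparisons among the active arms are intended as well as comparisons with control. The Discussion adds modified Baduanjin against resistance training and a possible synergy of the two.

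**Primary outcomes.** Outcome measurement says "Primary prognostic indicators included Lung function and 6MWT". For lung function, "TLC, VC, DLco, and min•mmHG are recorded in detail after the test"; none of these variables is put first. The abstract also counts HRCT among the main outcomes, while Outcome measurement makes it secondary.

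**Tests.** Statistical analysis specifies a 2 × 2 group × time ANOVA for the training effect, together with paired tests over time within each arm. It sets a two-sided 0.05. Data analysis repeats the rule: "P values less than 0.05 are considered significant".

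**Sample size.** The trial is sized on one pairwise 6MWT difference: "the minimum difference (miniDIFF) between different groups is 54 m, and the baseline standard deviation (SD) is 57 m", and "Given a two-tailed 0.05 and a power of 80%, the minimal sample size for each group is 19".

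**The concern.** With five arms there are ten possible pairs, and with two or more primary outcomes the number of tests that could carry the main claim multiplies. The article does not say which comparison on which outcome decides the trial, and its one significance rule applies to all of them alike. A difference between any two arms on any primary variable could then be reported as the trial's success, and that choice could be made after the data are seen. This matters because the stated goal is to prove an optimal exercise prescription, which is a confirmatory claim.

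The misfitting ANOVA makes it worse. Two arms by two time points suggests a series of pairwise analyses. Five arms by two time points would give one omnibus test per outcome. These readings have very different error rates, and the article does not say which is meant.

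**Working it through.** **1. The plan's own sample size.** Inputs from Sample size: difference 54 m, SD 57 m, two-sided 0.05, power 80%.

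- Normal formula: n = 2 × [57 × (1.960 + 0.842) / 54]² = 17.5, so 18 per group.
- Two-sample t-test: 18.5, so 19 per group, as stated.
- Loss of 30%: 19 / 0.70 = 27.1, which rounds up to 28, and 5 × 28 = 140. The article states 27 per group and 140 in total.

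The figure reproduces for one pair on one outcome at the full 0.05. Nothing is reserved for multiplicity.

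**2. Number of comparisons.** Pairs among five arms: 5 × 4 / 2 = 10. Comparisons with control: 4. Primary variables: two if lung function is a single outcome, four if TLC, VC and DLco are each tested beside 6MWT.

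**3. One outcome, exactly.** The ten pairs share arms, so 1 − 0.95¹⁰ = 40% is too high. With 19 per arm and a pooled SD, there are 5 × 19 − 5 = 90 degrees of freedom. The critical t is 1.987, and some pair reaches it when the studentized range of five means exceeds 1.987 × √2 = 2.81. That probability is 28%.

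**4. Several outcomes, by simulation.** Setting: no true difference, 19 completers per arm, normal outcomes with equal correlation r, and 20,000 runs per setting. One value per patient is compared; with two time points, a group × time interaction is a comparison of changes from baseline. The correlation is an assumption, since the article gives none.

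Chance of at least one p < 0.05 (rounded):

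| Outcomes | r | Ten pairs, ungated | Four vs CG, ungated | Omnibus 5 × 2 test, or pairs gated by it |
|---|---|---|---|---|
| 1 | – | 28% | 16% | 5% |
| 2 | 0 | 49% | 28% | 10% |
| 2 | 0.9 | 37% | 21% | 7% |
| 4 | 0 | 74% | 49% | 19% |
| 4 | 0.5 | 66% | 43% | 16% |
| 4 | 0.7 | 58% | 37% | 14% |
| 4 | 0.9 | 45% | 28% | 10% |

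Pooling the SD over five arms or using separate two-sample tests moves the ten-pair figures by about one percentage point. The within-arm paired tests are not counted here.

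**5. Power under error control.** For a 54 m difference, SD 57 m and 19 per arm (two-sample t-test):

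- alpha 0.05: 81%
- alpha 0.025: 72%
- alpha 0.01: 58%

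**The case against.** **The analysis may be gated.** The named test is an ANOVA, and 2 × 2 may be a slip for 5 × 2. There would then be one omnibus test per outcome, with a risk of 5% for one outcome. This stands as a possible reading, and the article never says that all ten pairs will be tested. It does not remove the problem: no gate is stated, the risk with more than one primary outcome still exceeds 5%, and an omnibus gate protects fully only when no arm differs at all.

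**A threshold of 0.05 does not exclude adjustment.** Adjusted p-values are also compared with 0.05, and post-hoc procedures are often left to a SAP, which is not at hand. This is fair. The article is silent on adjustment; it does not refuse it. But it publishes a general significance rule, an ANOVA that cannot hold five arms and a primary set without a lead variable. A SAP would have to correct these, not merely add detail.

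**Stronger readings to avoid.** A reader might infer that a false-positive claim is more likely than not, or that at least 40 primary tests are planned. The documents support neither. Forty tests (10 × 4) requires TLC, VC and DLco to be separate primary variables. Outcome measurement names only two primary indicators, and the lung function section also describes a three-level rating that could serve as one outcome. A risk above 50% needs all ten pairs tested ungated on three or more variables that are not very highly correlated, with no arm truly different. With two outcomes it stays at 37–49%.

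**Demoting lung function cuts against the aim.** The abstract's goal is to improve and protect lung function. This stands, so the fix offers a co-primary route.

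**Conclusion.** The concern holds in a conditional form. As published, the plan does not keep the false-positive risk of its main claim at 5%, because it fixes neither the primary comparison nor a lead lung function variable and states no gate or adjustment. How large the excess is depends on what the undefined analysis turns out to be:

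- **Pairs tested ungated:** from 16% (one outcome, comparisons with control only) or 28% (one outcome, ten pairs) to 37–49% for two outcomes over ten pairs and about 44–74% for four.
- **Omnibus test or gate:** nominal for one outcome, about 7–10% for two and 10–19% for four.

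These figures assume no true differences, 19 completers per arm, normal outcomes and correlations between 0 and 0.9. If some arms truly differ, fewer null comparisons remain and the ungated risk is lower. That the 2 × 2 layout does not fit five arms needs no assumption.

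**What to change.** Before unmasking, by amendment:

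1. Correct the between-group analysis to a 5 × 2 group × time ANOVA.
2. Name 6MWT distance, the only outcome the trial is sized on, as the primary outcome for the confirmatory claim.
3. Name the primary comparison(s). Test them in a fixed sequence at two-sided 0.05, stopping at the first non-significant step, or with Holm. The choice and order are the sponsor's; the document does not imply one.
4. Alternatively, keep lung function as co-primary: name one lung function variable and split alpha, for instance 0.025 each, with any further comparisons handled within each share.
5. Report all other pairs and outcomes with 95% confidence intervals as supportive, and make the abstract and Outcome measurement agree on HRCT.

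**Cost.** This is more than a change of wording. Recruitment is complete (Trial status), and the section on communicating amendments requires ethics committee approval and notification when outcome indicators change. For a 54 m difference with 19 per arm, the first step of a sequence keeps 81% power, but later steps may go untested. A 0.025 share gives about 72%. Holm over five comparisons, as an example, starts at 0.05 / 5 = 0.01, where power for a single comparison is about 58%. No further patients are needed if the sponsor accepts this.

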#### Subgroup analyses

Based on a previous statistical analysis of the results of pulmonary function tests, disease severity may be a potential factor contributing to the differences in outcome measures. Therefore, we considered performing corresponding subgroup analyses. Further subgroup analyses by sitting, standing, and lying will be considered to determine whether the effect of this exercise therapy on the treatment of IPF varies by posture.

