Surprisingly few studies have focused on the critically required positions for recovery in IPF patients who, to avoid exertional dyspnea, frequently adopt a sedentary lifestyle, which predictably results in extensive skeletal muscle degeneration, social isolation, and its negative psychological sequelae [19]. The inhaled and exhaled gases of 28 healthy participants are collected for 45 min (15 min in each position) while they performed three different positions (lying, sitting, standing) in random order. It is determined that standing expends more energy than lying down or sitting, and patients with IPF are frequently forced to sit or lie down to avoid shortness of breath due to impaired lung function [20]. Patients with IPF are significantly less active than their age-matched healthy counterparts. As sedentary time increased, its lower daily physical activity led to a significant decline in survival [21]. The traditional Baduanjin has only one standing position, indicating that we must not only develop a pulmonary rehabilitation program that allows IPF patients to exercise while sitting or lying down in addition to standing, but also minimize prolonged sitting or lying down time in order to improve IPF patient survival. Liu et al. develop a simplified Baduanjin exercise scheme.

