In this study, three distinct forms of Baduanjin, including sitting horizontally and vertically, are developed to accommodate IPF patients with varying disease severity; each form has its own distinctive characteristics. As an illustration, the seventh form of the vertical Baduanjin is a combination of the traditional Baduanjin and the “tiger rushing” movement in Wuqinxi. During the exercise, the hands are presented in the form of “tiger claws”, raised to the chest with a deep inhalation to make the sound of “si”, and the process of pushing the hands forward with force, accompanied by the exhalation of the gas, “hu” the sound of. Throughout the breathing process, when inhaling, the diaphragm and intercostal muscles contract, causing the anteroposterior, left and right, and superoinferior diameters of the thoracic cavity to increase, and the thoracic volume expands, causing the air pressure in the lungs to be lower than the outside atmospheric pressure, forming an active inhalation movement. When exhaling, the diaphragmatic muscles and external intercostal muscles relax, causing the thoracic volume to shrink and the lungs to retract, causing the air pressure in the lungs to be greater than the outside air pressure, resulting in passive exhalation. The combination of exhalation exercise and inhalation exercise maintains the continuity and patency of breathing. There is experimental evidence to show that when IPF patients are breathing, the activity rate of the diaphragm is lower than that of the healthy control group, especially when taking a deep breath. To achieve the effect of improving pulmonary ventilation [22]. This may fulfill the function of acute oxygen supplementation, which increases supplemental oxygen tolerance and alleviates dyspnea in individuals with idiopathic pulmonary fibrosis who do not have hypoxemia at rest [23]. At the same time, hypoxia may be related to the peripheral skeletal muscle dysfunction observed in IPF patients [24], so in the rehabilitation of IPF patients, hypoxia and skeletal muscle may have a mutual influence rather than an independent relationship. The fifth pose of Sitting Baduanjin is a combination of the traditional Baduanjin and Yijinjing movements of “drawing the knife”. Place one hand on the neck and the other on the waist and perform the exercise with comparable force using both hands. Through the external and internal rotation of the arms, similar to the action of expanding the chest, the intercostal muscles are contracted and the ribs are lifted, causing the anteroposterior, left and right, and superoinferior diameters of the thoracic cavity to expand and contract, delaying the reduction of chest-related muscles. Studies have confirmed that when the thoracic skeletal muscle mass of IPF patients reaches the level of low muscle mass, it is positively correlated with the quality of survival and prognosis of the patients. Therefore, the exercise of the thoracic skeletal muscle can improve the quality of life and the prognosis of patients [3]. The eighth form of horizontal Baduanjin is “bend the knee joint and dorsi-extend the foot joint”, which is to carry out related exercises for the patient’s limb function. During this session, engage the relevant limb muscles by flexing the knee and hooking the foot to prevent and improve muscle atrophy. Modern research has demonstrated that, with regard to skeletal muscle, appropriate exercise training can have an effect on peripheral skeletal muscle strength and limb mobility [25]. Simultaneously, the majority of anti-fibrotic IPF patients died of chronic respiratory failure; skeletal muscle loss is observed in these individuals, but there is no significant weight loss, which displays that preventing skeletal muscle atrophy in IPF patients is crucial [26].

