## Discussion

Dyspnea is a typical feature of IPF. In clinical practice, the majority of IPF patients experience varying degrees of limb function degradation as the disease progresses. Therefore, it is of utmost clinical importance to treat dyspnea and improve or enhance the limb function of IPF patients.

Baduanjin is a gentle, safe, and effective traditional Chinese sport. Compared with the traditional Baduanjin, the Modified Baduanjin has the following important characteristics: (1) Easy to operate, simple and interesting action, at the same time, we combined the features of the Modified Baduanjin to remember the name. (2) Easy to develop, the Modified Baduanjin has extremely low needs for the environment and site and does not borrow any tools. It can be carried out effectively at home, in the office, and even in a hospital bed. (3) Suitable for prevention, treatment, and rehabilitation of IPF, can be used in the complete process of IPF disease, and according to the severity of the disease, can choose different kinds of vertical, seated, and horizontal training. It is convenient for doctors to carry out their duties. Doctors can use the Modified Baduanjin in the propaganda, education, and prevention and treatment of IPF diseases. Patient training at the same time can promote communication between patients and patients, patients and doctors, compared with drug therapy, no pain, this is a natural, pollution-free, easy, and pressure-free new way of prevention and treatment. This study, therefore, focuses on the lung function and limb motor function of stable IPF patients and measures the effect and effect of Modified Baduanjin on IPF patients using different indicators.

Rehabilitation exercise is an important part of IPF treatment. Anti-resistance exercise stimulates and trains the muscles related to IPF rehabilitation through a variety of tools, such as instruments, weight lifting, rubber bands, and so on, to improve the skeletal muscle strength and function of IPF patients. COPD patients who use rubber band exercises can improve their 6MWT test results, according to studies. We hope to examine the effect of anti-resistance exercise on IPF patients and compare its therapeutic effect to that of Modified Baduanjin in order to determine its specific effect and effect on stable IPF.

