Resistance movement is characterized by setting relevant resistance movements for the relevant ten muscles, to improve the muscle strength and function of the relevant muscles, and to improve lung function and limb movement function. The Modified Baduanjin is a combination of whole-body aerobic exercise and breathing that can effectively improve dyspnea and limb movement ability. Consequently, we hypothesize that this combined exercise regimen may have a synergistic effect on IPF patients.

This study has several bright spots. First, the Modified Baduanjin is innovatively developed in three forms, standing, sitting, and horizontal, compared with traditional Chinese sports skills. As far as we know, the latter two forms are new forms that are not available in other exercise therapies. Therefore, patients with severe lung function injury, particularly long-term hospitalized patients, can choose the appropriate sitting or horizontal rehabilitation posture, which is not possible with other exercise therapies. Second, for IPF patients, we evaluate several comprehensive indicators of new-type Baduanjin on IPF in the stable phase, paying special attention to lung function and limb function. Third, a subgroup analysis of patients with different degrees of disease is conducted to study whether there are differences in the therapeutic effects of vertical, sitting, and horizontal types respectively, and finally to find out the best combination plan to optimize the therapeutic effect. Finally, this study is conducted strictly and standardized under CONSORT guidelines [34], to explore the therapeutic effect of Modified Baduanjin on stable IPF patients.

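### The standing, sitting and lying comparison is non-randomised and probably confounded by disease severity, so it cannot identify the best combination of forms

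*Protocol article*

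**What the plan says.** All references are to the protocol article.

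- **Planned analysis.** Subgroup analyses first names disease severity as a possible driver of outcome differences and considers subgroups for it. It then adds: "Further subgroup analyses by sitting, standing, and lying will be considered to determine whether the effect of this exercise therapy" differs with posture.
- **Intended conclusion.** The Discussion lists as a strength a subgroup analysis in patients with different degrees of disease, which is meant to show "whether there are differences in the therapeutic effects of vertical, sitting, and horizontal types respectively, and finally to find out the best combination plan".
- **What is randomised.** Under Randomization and concealed allocation, "participants will be randomized into five groups: CG, IG, TG, RG, and IRG". No section allocates posture by chance.
- **Where the forms exist.** Background says: "The traditional Baduanjin has only one standing position". The control group (CG) does no exercise, and the resistance group (RG) does muscle-based resistance work with no Baduanjin form. Only IG and IRG use modified Baduanjin, and neither intervention section says who performs which form.
- **What determines the form.** Background says the three forms "are developed to accommodate IPF patients with varying disease severity". The Discussion says that users, "according to the severity of the disease, can choose different kinds of vertical, seated, and horizontal training", and that patients with severe lung function injury "can choose the appropriate sitting or horizontal rehabilitation posture".
- **Severity subgroup.** Statistical analysis separately describes a pre-designated subgroup analysis by disease severity.

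**The concern.** A subgroup analysis of a randomised trial is protected when the subgroup is fixed before allocation and exists in every arm. Posture appears to meet neither condition. It is part of the treatment received, and sitting and lying have no counterpart in CG, RG or TG. What remains is a comparison of patients within IG and IRG who used different forms. If the form tracks severity, that comparison sets milder patients against sicker ones, and the article itself names severity as a likely source of outcome differences.

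At stake is a prescription claim. A difference produced by who uses each form could be published as evidence on which form, or mix of forms, works best.

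**Working it through.** **1. The plan's own figure.** Inputs from Sample size: difference 54 m, SD 57 m, two-sided 0.05, power 80%.
- Normal approximation: n = 2 × [57 × (1.96 + 0.84) / 54]² = 17.5, so 18 per group. The t-test version gives 18.5, so 19, as stated.
- Allowing for 30% loss: 19 / 0.7 = 27.1. The article gives 27; rounding up gives 28, and 5 × 28 = 140, the stated total.

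The sample size reproduces, so the point does not rest on an arithmetic error there.

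**2. Which randomised contrasts exist for each posture.**

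| Arm | Standing | Sitting | Lying |
|---|---|---|---|
| CG | no exercise | no exercise | no exercise |
| TG | yes | no | no |
| RG | no Baduanjin form | no Baduanjin form | no Baduanjin form |
| IG | assignment not stated | assignment not stated | assignment not stated |
| IRG | assignment not stated | assignment not stated | assignment not stated |

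For sitting or lying, the only contrast between arms is IG against IRG. That concerns adding resistance training, not posture.

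**3. Precision of a posture comparison.** Assumptions: even split over three postures; baseline SD of 57 m used as the outcome SD (no SD of change is given); equal arms. For n patients per posture, half-width = t × 57 × √(2/n), with 2n − 2 degrees of freedom.

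| Patients used | n per posture | SE (m) | t | Half-width (m) |
|---|---|---|---|---|
| IG, 28 enrolled | 9.3 | 26.4 | 2.11 | about 56 |
| IG, 19 completers | 6.3 | 32.0 | 2.2 | about 70 |
| IG + IRG, 56 enrolled | 18.7 | 18.7 | 2.03 | about 38 |
| IG + IRG, 38 completers | 12.7 | 22.6 | 2.07 | about 47 |

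Power to detect 54 m between two postures is 49%, 34%, 80% and 63% in the same order. Pooling improves precision but mixes two different regimens.

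**4. What confounding could do.** The training effect is analysed as group × time. If posture is handled the same way, fixed baseline differences between mild and severe patients cancel. Bias arises only if change over three months differs by severity, including through regression to the mean.

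A simulation (4,000 runs per setting) took 19 IG completers, three equally likely severity levels, SD 57 m and no true posture effect. The severity gap is the assumed mildest-to-sickest difference in the analysed quantity; under group × time, read it as a difference in change.

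| Assumed gap (m) | Form always follows severity: spurious difference, false-positive rate | Form follows severity in 80%, random in the rest | Form random |
|---|---|---|---|
| 15 | 14.6 m, 7% | 12.5 m, 7% | about 0, 5% |
| 30 | 30.1 m, 13% | 24.4 m, 10% | about 0, 5% |
| 54 | 53.8 m, 31% | 42.7 m, 21% | about 0, 5% |

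When the form always follows severity, the posture contrast returns the severity gap itself. The gaps are illustrative; the article gives none.

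**The case against.** The strongest reply has four parts.

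- **The mechanism is inferred.** A reader might take it as established that form is chosen by severity after allocation. The documents do not support that. The IG and IRG sections give no assignment rule or timing, Background gives design intent, and the Discussion passages describe the programme's general merits. A condensed article may also leave assignment to the full protocol. This stands, and it limits the claim to probable confounding. It does not rescue the analysis: no section randomises posture, and if every patient performed all three forms, posture subgroups could not be formed.
- **The Discussion may intend comparisons within severity levels.** Its sentence does begin with patients of different degrees of disease. That reading would reduce the confounding, but the comparison would remain non-randomised and the cells would be smaller still.
- **The analysis is tentative.** It is only to be considered, and neither the sample size nor the main analyses depend on it. This is fair on power. An exploratory label does not remove confounding, and the Discussion states its aim without that caution.
- **The pessimistic precision figures use completers.** An intention-to-treat analysis is planned, so the range from 28 enrolled to 19 completers per arm is the fair statement.

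A reader might also infer that sitting and lying will look worse, or that the five-arm comparison or the severity subgroup is compromised. None of these follows. The direction of bias is unknown, the arm comparisons are randomised, and comparisons within baseline severity strata stay randomised if severity is measured before allocation.

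**Conclusion.** The concern holds in a limited form. The article considers a posture comparison and draws from it an aim that the design cannot support. The comparison is non-randomised because only the arms are randomised and sitting and lying exist only in IG and IRG. Confounding by severity is likely rather than proven, acts through differential change, and does not shrink with sample size.

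Imprecision is secondary. The half-widths of 56 to 70 m within IG and 38 to 47 m pooled rest on an even posture split, equal arms and the baseline SD standing in for the outcome SD. Within IG the interval is wider than the 54 m planning difference on either side; pooled, it is somewhat narrower than that. The primary analysis is unaffected. The wording should be corrected because a headline claim about prescribing depends on it.

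**What to change.** 1. **Subgroup analyses.** State that the posture used will be reported descriptively, as exploratory, with no test between postures.
2. **Effect modification.** Use the severity subgroup already planned in Statistical analysis, run as an arm × baseline-severity interaction across all five arms. Write down the severity measure and take it from data collected before randomisation. A continuous lung-function measure is preferable: it uses 4 interaction degrees of freedom, against (5 − 1) × (3 − 1) = 8 for three severity levels.
3. **Timing of baseline.** Reconcile Randomization and concealed allocation, which puts randomisation before the baseline assessment, with Data collection and management, which says the reverse. Item 2 depends on the answer.
4. **Discussion.** Delete the claim that comparing the forms will find the best combination.

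Recruitment is reported as complete, so posture cannot now be randomised for these patients, but wording and analysis can still change. The cost is small: no inferential claim about which posture is best, and an interaction test that is itself weak. For illustration, with two arms and two equal severity strata the interaction SE is 57 × √(4 / (n/2)). That is 37.0 m at n = 19 per arm and 30.5 m at n = 28, giving about 31% and 43% power for a 54 m difference in effect.
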